## Discussion

Regular screening of symptoms by the use of PROs and access to resources for coping skills could help to detect and/or manage symptoms that up to a quarter of patients with lymphoma are experiencing.

The results of the LIVE trial will provide novel insights into whether access to PRO feedback and the *Living with lymphoma *intervention will be effective in increasing self-management skills and satisfaction with information, and reducing psychological distress. Since one third of patients will be randomised to solely access to PRO feedback and not to the *Living with lymphoma *intervention, it will be possible to investigate the superiority of access to PRO feedback as well as the superiority of access to PRO feedback and the *Living with lymphoma *intervention compared to standard care.

The LIVE trial is embedded in the population-based PROFILES lymphoma registry, which provides a unique setting to ascertain information on response, uptake, and characteristics of patients with lymphoma in web-based intervention(s). This information is important with respect to the generalisability of results and, moreover, it demonstrates which patient subgroups will benefit most from PRO feedback and the *Living with lymphoma *intervention*.* Patients will not be selected based on their symptoms or distress level prior to study entry and it is up to patients themselves how, and to what extent, they use the intervention(s). When effective, access to PRO feedback and the *Living with lymphoma *intervention could serve as easily and widely accessible interventions for coping with lymphoma in the Netherlands.

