**Methods/design:**

The LIVE randomised controlled trial consists of three arms: (1) standard care, (2) PRO feedback, and (3) PRO feedback and the *Living with lymphoma *intervention. Patients who have been diagnosed with Hodgkin lymphoma, non-Hodgkin lymphoma, including chronic lymphocytic leukaemia, as registered in the Netherlands Cancer Registry in various hospitals will be selected for participation. Patients are invited via their haemato-oncologist 6 to 15 months after diagnosis. The PRO feedback includes a graphical overview of patients’ own symptom and functioning scores and an option to compare their scores with those of other patients with lymphoma and a normative population of the same age and sex. The *Living with lymphoma *intervention is based on cognitive behavioural therapy components and includes information, assignments, assessments, and videos. Changes in outcomes from baseline to 16 weeks, 12, and 24 months post intervention will be measured. Primary outcomes are self-management skills, satisfaction with information, and psychological distress. Secondary outcomes are health-related quality of life, illness perceptions, fatigue, and health care use.

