### Statistical analyses

All statistical analyses will be performed using Statistical Analyses Software (SAS; version 9.4 for Windows, SAS Institute Inc., Cary NC, USA). Analyses on effectiveness of the intervention will be primarily done according to intention-to-treat methodology. Second, per-protocol analysis will be performed to analyze the efficacy of the intervention. All statistical tests will be two-sided and considered significant if *p* < 0.05.

Missing outcome data will be assumed to be ‘missing at random’ (MAR), conditional on key predictors of ‘missingness’ (in particular, baseline values of the outcome variables of interest, and study arm).

Patients’ sociodemographic and clinical variables will be compared at baseline between the three study arms using chi-square analyses for categorical variables and ANOVA for continuous variables and will be analysed as covariates.

Repeated measures analysis using generalised estimating equations, which account for the intra-patient dependency of the repeated measures, will be used to analyse the effect of the intervention on the outcome variables. We will investigate differences in effect of the two intervention arms and the arm receiving standard care at the different time points. Differential effects of the intervention arms by age, cancer subtype, and baseline levels of the outcomes of interest will be assessed for the outcome measures by adding terms for the interaction between age, cancer subtype, baseline levels, and care arm to the regression models.

Routinely collected data from the population-based NCR on patient and tumour characteristics will enable us to compare paper-and-pencil respondents with online respondents, as well as respondents with nonrespondents and patients with unverifiable addresses in order to determine the external validity of the results and answer our second study objective.

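### The Discussion says response and uptake data will demonstrate which subgroups benefit most; such data cannot show this, and the planned interaction tests can only explore it

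*Protocol article*

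**What the plan says.** The third paragraph of the Discussion explains that placing the trial inside the PROFILES lymphoma registry "provides a unique setting to ascertain information on response, uptake, and characteristics of patients with lymphoma in web-based intervention(s". The next sentence refers back to that information, calls it important for generalisability, and adds that "it demonstrates which patient subgroups will benefit most from PRO feedback and the" *Living with lymphoma* intervention.

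Outcome-based subgroup analysis appears only under Statistical analyses: "Differential effects of the intervention arms by age, cancer subtype, and baseline levels of the outcomes of interest will be assessed for the outcome measures", and this is to be done "by adding terms for the interaction between age, cancer subtype, baseline levels, and care arm to the regression models". The same section sets one decision rule for everything: "All statistical tests will be two-sided and considered significant if *p* < 0.05".

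The Sample size calculation section adjusts alpha for the three primary outcomes only, and arrives at 222 patients (74 per arm) from a medium overall effect of 0.25 in a repeated measures ANOVA. It contains no interaction with a patient characteristic. Objectives and hypotheses contains no subgroup hypothesis.

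**The concern.** Two things do not fit together. First, the evidence named for the subgroup statement is of the wrong kind. Response and uptake show who joins and who uses the website. Whether one group gains more than another is a question about the difference in outcome between randomised arms, compared across groups. A group can use the website heavily and gain nothing from it, or use it little and gain much.

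Second, the analysis that is of the right kind is not strong enough for the verb *demonstrates*. It is a set of interaction tests over several modifiers and outcomes, each judged at 0.05, in a trial whose size was not set with interactions in mind.

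At stake is what the trial may conclude. The primary comparison is untouched, but a finding about who benefits most could be presented as established when the design can only suggest it.

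**Working it through.** **1. Claim against source.** The Discussion draws differential benefit from response, uptake and characteristics. The last paragraph of Statistical analyses uses registry comparisons (online v paper respondents, respondents v nonrespondents) to judge external validity, which is what they can support. Neither source contains an outcome contrast between arms. The Discussion also says that patients themselves decide how far they use the interventions, so use is self-selected. This step needs no arithmetic.

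**2. What 222 was sized for.** For repeated measures ANOVA, between factors, with 3 groups, m = 2 measurements and f = 0.25, the noncentrality is f² × N × m / (1 + (m − 1) × rho). With alpha = 0.05/3 = 0.0167 and rho = 0.7 (assumed; the article gives none) it is 0.0625 × 222 × 2 / 1.7 = 16.3. The smallest balanced N with 90% power is then 222 (power 0.902). The stated figure is therefore reproduced as the size for an overall difference between arms. (The article prints 0.167; that is a separate matter.)

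**3. Number of tests.** The article gives no count. There are three modifiers: age, cancer subtype and baseline level. With one score per outcome and one joint test per modifier:
- three primary outcomes: 3 × 3 = 9 tests;
- seven outcomes as listed in the abstract (three primary, four secondary): 3 × 7 = 21 tests;
- ten instruments as listed under Study outcome measures (three primary, seven secondary): 3 × 10 = 30 tests.

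Separate scales, arm contrasts or time points would raise these counts.

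**4. Chance of at least one significant interaction when nothing differs.** For k independent tests it is 1 − 0.95^k: 37.0% for 9, 65.9% for 21 and 78.5% for 30. Outcomes are correlated, so two simulations were run. One uses equicorrelated normal test statistics within each modifier. The other uses patient-level data: 1,500 trials of 222 patients, pre-post correlation 0.5, four subtypes with assumed shares of 15/35/30/20%, and joint F tests.

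| Outcome correlation | 9 tests, statistics | 9 tests, patients | 30 tests, statistics | 30 tests, patients |
|---|---|---|---|---|
| 0.3 | 35.6% | 36.1% | 72.5% | 76.1% |
| 0.5 | 33.1% | 33.3% | 63.8% | 68.8% |
| 0.7 | 29.2% | 30.1% | 51.3% | 57.6% |

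The range is therefore about 30-37% for 9 tests and about 51-79% for 30. At a correlation of 0.8, 30 tests give 43%. The expected number of false interactions is 9 × 0.05 = 0.45 or 30 × 0.05 = 1.5.

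**5. Power for a true difference in effect.** Take two arms of 74, each split into equal halves of 37, one follow-up adjusted for baseline, and outcome SD 1. The standard error of the difference in effect is 2 × √(2(1 − rho²)/74), and power is Φ(0.5/SE − 1.96). The 0.5 SD is the plan's own threshold for a clinically important difference.
- rho = 0.3: SE 0.314, power 36%
- rho = 0.5: SE 0.285, power 42%
- rho = 0.7: SE 0.235, power 57%

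Unequal groups, or patients lost from the 74 per arm, would lower these figures.

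**The case against.** The strongest reply is that the offending words are one sentence in a Discussion, while the analysis section uses the right tool, arm-by-modifier interactions with modifiers named in advance. Exploratory labels and multiplicity for subgroup analyses are commonly left to a statistical analysis plan, which is not shown. No hypothesis or effectiveness criterion depends on a subgroup.

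Much of this stands. The missing label is not itself a fault, and the two parts must be kept apart: the false-positive rates measure the interaction tests, not the use of uptake data. The Discussion sentence, however, is a positive statement that an analysis plan would not repair, and the 0.05 rule is stated for all tests.

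A reader might also infer more than the article supports:
- *That one significant interaction will be reported as a subgroup that benefits most.* No section says so. The plan says that differential effects will be assessed.
- *That there are at least 30 tests, so a false subgroup appears in most trials.* Thirty is a count from the list of instruments, not a minimum. On the three primary scores it is 9 tests and about 30-37%. Some instruments also do not yield one common score: health care use is a set of single items, and the lymphoma module differs by subtype.
- *That most real differences would be missed.* At a pre-post correlation of 0.7 the power is 57%. The calculation is also a simplification, since the plan specifies repeated measures regression, in which age and baseline level can stay continuous.
- *That the claim would decide who is offered the interventions.* The Discussion foresees wide access and proposes no targeting.

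**Conclusion.** The point holds as a mismatch between a stated conclusion and what the design can deliver. Response and uptake data cannot show differential benefit at all. The interaction tests can address it, but only tentatively: with no true difference, at least one is significant in about 30-37% of trials with 9 tests and about 51-79% with 30, and power for a 0.5 SD difference in effect is about 36-57%.

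The first part rests on the text alone. The rates rest on assumptions: one score per outcome, one joint test per modifier, outcome correlations from 0 to 0.7, and the assumed subtype shares in the patient-level runs. The power figures assume equal halves, 74 v 74 patients, one follow-up and pre-post correlations of 0.3 to 0.7. Under all of these, *demonstrates* is too strong. The point does not bear on the primary comparison.

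**What to change.** **Discussion.** Say that response and uptake data describe reach and generalisability. Say that differential benefit is explored through the interactions set out under Statistical analyses and is hypothesis-generating. Drop the claim to demonstrate which subgroups benefit most.

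**Statistical analyses.** Exempt the interaction tests from the general 0.05 rule as a basis for claims and label them exploratory. Report interaction estimates with 95% confidence intervals and the number of tests done.

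Restricting the interactions to the primary outcomes, or asking for p below 0.05/9 before any subgroup statement, would be reasonable but optional. Neither is needed to correct the text, and a stricter threshold would lower power that is already limited.

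**Cost.** Wording only, with no change to data collection or sample size. The price is a weaker subgroup claim.

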### Trial status

Recruiting.

## Abbreviations

BREATH: BREAst cancer e-healTH
CBT: Cognitive behavioural therapy
CLL: Chronic lymphocytic leukaemia
HL: Hodgkin lymphoma
HRQoL: Health-related quality of life
ICD-O-3: International Classification of Diseases for Oncology, third edition
IKNL: Netherlands Comprehensive Cancer Center
LIVE: Lymphoma InterVEntion
MAR: Missing at random
NCR: Netherlands Cancer Registry
NHL: Non-Hodgkin lymphoma
PRO: Patient-reported outcome
PROFILES: Patient Reported Outcomes Following Initial treatment and Long-term Evaluation of Survivorship
SAS: Statistical Analyses Software
